### Study Procedure and Outcome Measures

Table 3 shows the study schedule for enrollment and assessment, which may take between 0.5 hours and 1 hour in a single visit. The assessment and evaluations will take place in a temperature-controlled environment of 25 °C. The study team has undergone training by the principal investigator on the use of questionnaires, pulse sphygmograph, and tongue diagnostic devices to reduce interphysician variability.

**Table 3 table3:** The study schedule.

		Enrollment	Allocation	Postallocation	
Timepoint		–*t*_1_	0	*t* _1_	*t* _2_
**Registration**					
	Digital registration	✓			
**Enrollment**					
	Informed consent	✓			
	Eligibility screen	✓			
	Allocation		✓		
Intervention				N/A^a^	N/A
**Assessment procedure (0.5-1 hour)**					
	Health evaluation (vital signs, blood sugar levels, BMI, medications, symptoms)			✓	
	Questionnaires (Physical Activity Questionnaire, Sugar Intake, and CCMQ^b^)			✓	
	Pulse diagnosis				✓
	Tongue diagnosis imaging				✓

^a^N/A: data are not applicable or not available.

^b^CCMQ: Constitution in Chinese Medicine Questionnaire.

#### Health Evaluation

Each participant’s age, sex, ethnic race, body weight, height, blood sugar level (including blood glucose in fasting, 2hPG or HbA_1c_ results if available from the patient’s regular blood test report), and health status, including medication prescription, will be recorded. Participants who have been clinically diagnosed as prediabetic or diabetic will be asked to present their blood test results from 3 months prior to or after the assessment date. The study team will contact the participant following the study if the blood test results are not available at the time of assessment. The primary objective of collecting these data is to enable the study team to determine whether the diabetic or prediabetic disorders are under control and if there is a correlation with the syndrome being studied. The information that will be gathered is as follows.

Vital signs: The Omron Automatic TIC Blood Pressure Monitor HEM-7130 will be used to assess vital signs, including systolic blood pressure, diastolic blood pressure, and pulse rate.BMI: After measuring height and weight, the BMI will be calculated and documented.Medications: Western and Chinese medications consumed by the participant will be recorded to identify possible interventions and correlations for TCM syndrome differentiation.Existing symptoms will be collected to determine the potential correlation with TCM syndrome differentiation.

#### Physical Activity Questionnaire and Sugar Intake

The Physical Activity Questionnaire, adapted and modified from the Singapore Prospective Study Program Physical Activity Questionnaire, will be used to record the level of physical activity during the past 3 months. The Singapore Prospective Study Program Physical Activity Questionnaire evaluates physical activities including transportation, leisure time activities, occupational physical activities, and household activities. This questionnaire was validated against the International Physical Activity Questionnaire in a multiethnic population of Chinese, Malays, and Indians residing in Singapore. It was concluded to show good validity and repeatability for vigorous activities [38].

Metabolic equivalent task (MET) levels will be used to compare the average energy expenditure in each group. The 1 MET unit, which represents the energy expended while sitting quietly, is equivalent to 3.5 ml of O_2_ per kg body weight per minute or 1.2 kcal per minute for a 70-kg individual [39]. Moderate intensity refers to physical activity that is performed between 3 and <6 times the intensity of rest (METs), while vigorous intensity is defined as physical activity that is performed at 6.0 or more METs [38]. The WHO Physical Activity Guidelines (2020) recommend a minimum of 150-300 minutes of moderate-intensity aerobic physical activity per week and engaging in muscle-strengthening activities at moderate or greater intensity on at least 2 days a week to stay physically active [40]. Those who reach a high level of physical activity per week perform vigorous-intensity activity on at least 3 days of 1500 MET-minutes per week, or 7 or more days of activities of a minimum of 3000 MET-minutes. While those with a moderate level of physical activity per week perform 3 or more days of vigorous-intensity activity of at least 20 min/day, or 5 or more days of moderate-intensity activity of at least 30 min/day, or 5 or more days of activities achieving a minimum of at least 600 MET-minutes/week. Participants who do not meet any of the above criteria would be considered inactive.

Additionally, weekly sugary food and beverage consumption will be documented. This will aid in identifying the risk variables involved and the association between the body constitutions and various forms of “*xiao-ke*” based on TCM syndrome differentiation.

#### The Constitution in Chinese Medicine Questionnaire

Based on TCM principles, the Chinese Medicine Questionnaire (CCMQ), which was established in 2009 by the China Association of Chinese Medicine, will be used to evaluate the body constitution of each participant. This questionnaire consists of 60 questions divided into nine categories of body constitution: (1) balanced, (2) qi deficiency, (3) yin deficiency, (4) yang deficiency, (5) phlegm dampness, (6) damp heat, (7) blood stasis, (8) qi stagnation, and (9) inherited special constitution. Each category has 7 or 8 questions. A 5-point Likert scale that quantitatively assesses the body characteristic is adopted, and the original score is obtained by summing the categorized items. The adjusted score is derived by: 100 [(original score – number of questions) / (number of questions 4)]. The scoring algorithm indicates the likelihood of a particular type of body constitution with a higher score. A subscale criterion of at least 30 points will be used to classify the body composition [41]. Table 4 provides the recommended assessing criteria [42].

Lu et al [41] concluded that the CCMQ is capable of measuring the 9 body constitutions with reasonably good construct validity and reliability. Another study reported that the reproducibility using the Spearman correlation coefficient for the subscales ranged from 0.76 to 0.90, indicating good repeatability and quantitativeness [43].

**Table 4 table4:** Assessing criteria of CCMQ^a^.

Adjusted score of balanced constitution	Total adjusted score of 8 unbalanced constitution	Body constitution
≥60	<30	Balanced constitution
≥60	30-39	Balanced constitution but leaning toward the unbalanced constitution with a score ≥40
≥60	≥40	Unbalanced constitution with a score ≥40
<60	≥40	Unbalanced constitution with the highest score
<60	30-39	Prone to an unbalanced constitution with the highest score

^a^CCMQ: Constitution in Chinese Medicine Questionnaire.

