### Statistical Analyses

The baseline variables (age, sex, height, body weight, BMI, and blood sugar levels), MET-minutes for physical activity, scoring of body constitution, pulse assessments, and tongue analysis results will be compared between the five groups.

Using ANOVA, we will compare the variances across the means of the SE_13-50 Hz_ value from the pulse sphygmograph between each group and the control. Analysis of covariance will also be used to assess the group differences while controlling for potential confounding variables such as gender, age, BMI, physical activity levels, and others. Using the Bonferroni test for post hoc multiple comparisons, the mean values will be compared and corrected. Chi-square tests will also be used to do the comparative analysis of the body constitutions or syndromes between the objective and subjective assessments. All tests will be 2-tailed and *P*<.05 will be considered statistically significant. We will use STATA (standard edition version 18.0; StataCorp LLC) for the analysis.

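### The CCMQ classification rule in Table 4 cannot be applied as printed: one row contradicts itself, the score column is misnamed, and some attainable scores have no class

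*Protocol article*

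**What the plan says.** The rule is in the protocol article, section The Constitution in Chinese Medicine Questionnaire, in the text and Table 4.

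- Scoring: "Each category has 7 or 8 questions"; "A 5-point Likert scale that quantitatively assesses the body characteristic is adopted"; and "The adjusted score is derived by: 100 [(original score – number of questions) / (number of questions 4". The multiplication signs were lost when the PDF was read, which is not a fault of the plan.
- Cut-off in the text: "A subscale criterion of at least 30 points will be used to classify the body composition".
- Table 4 crosses the balanced score with a second column headed "Total adjusted score of 8 unbalanced constitution". It has five rows. The second, for balanced ≥60 and unbalanced 30-39, is labelled "Balanced constitution but leaning toward the unbalanced constitution with a score ≥40". The last, for balanced <60 and unbalanced 30-39, is labelled "Prone to an unbalanced constitution with the highest score".

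The result is used in several places. Under Statistical Analyses, "scoring of body constitution, pulse assessments, and tongue analysis results will be compared between the five groups", and chi-square tests are planned on constitutions or syndromes. Under Syndrome Differentiation, the CCMQ is one of three inputs to the xiao-ke classification. Under Tongue Diagnosis, device results are to be reconciled with it.

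**The concern.** A classification rule should give every participant exactly one result, and two people scoring the same questionnaire should agree. Table 4 does not meet that standard. One row names a constitution that its own condition rules out, the quantity in the second column is unclear, and some score patterns match no row. Whoever does the scoring must then repair the rule, possibly after seeing data. The category counts in the chi-square tests, and the CCMQ contribution to the syndrome label, would depend on that unrecorded repair. A difference in constitution from healthy participants is among the findings the Discussion anticipates, so the rule matters to what the study will report.

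**Working it through.** **Inputs.** All come from the CCMQ section: k = 7 or 8 items per category, and five response levels, taken as 1 to 5 because the formula subtracts one point per item. With the multiplication signs restored:

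adjusted score = 100 × (raw − k) / (4 × k)

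Raw = k gives 0 and raw = 5k gives 100, so scores run from 0 to 100 and are never negative. One step on one item is worth 100/28 = 3.571 points (k = 7) or 100/32 = 3.125 points (k = 8).

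**Attainable values near the cut-offs**

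| k | last value below 30 | values from 30 to 39 | between 39 and 40 | first value ≥40 |
|---|---|---|---|---|
| 7 | 28.57 | 32.14, 35.71 | 39.29 (raw 18: 100 × 11/28) | 42.86 |
| 8 | 28.13 | 31.25, 34.38, 37.50 | none | 40.63 |

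**Row 2.** If the column is a sum, eight non-negative scores adding to 30-39 cannot include one above 39. If it is the highest subscale, a maximum of 30-39 means that none reaches 40. The constitution named in the label cannot exist under either reading.

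**Column header.** A sum of eight scores runs from 0 to 8 × 100 = 800, and a sum of 40 is a mean of 40/8 = 5 per subscale. Eight 7-item subscales at 28.57, all below 30, add to 8 × 28.57 = 228.6. Read literally, that person falls in the ≥40 rows. With balanced ≥60, row 3 then points to a constitution scoring at least 40, and there is none. The subscale criterion in the text and the single-constitution labels in the rows fit a per-subscale reading. The header does not.

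**Missing class.** Two balanced bands × three unbalanced bands = 6 cells.

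| | unbalanced <30 | 30-39 | ≥40 |
|---|---|---|---|
| balanced ≥60 | row 1 | row 2 | row 3 |
| balanced <60 | **no row** | row 5 | row 4 |

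The empty cell can be reached. On 8 items, a balanced raw score of 27 gives 100 × 19/32 = 59.4. Nine categories of 7 or 8 items need 63 to 72 item slots, but there are 60 questions, so some items must be shared. If a balanced item also counts in an unbalanced subscale, its worst answer adds 4 steps, which is 12.5 points (k = 8) or 14.3 points (k = 7). Two such items on one subscale add at most 28.6, still below 30. The cell is therefore attainable unless three or more heavily scored shared items sit on the same subscale; the article does not give the item allocation.

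**Band edges.** A highest subscale of 39.29 is above 39 and below 40. It matches no row at either level of the balanced score.

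**Text against table.** Take balanced ≥60 and a highest subscale of 35.71. The 30-point criterion in the text is met, yet Table 4 calls the person balanced with a leaning and uses an unqualified unbalanced label only from 40. The article does not say whether 30 marks a tendency or a classification.

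**The case against.** The best defence is that a reader who knows the instrument would see what is meant. The section speaks of a subscale criterion, the labels name single constitutions, and the header is loose wording. This is an exploratory observational study, the sample size reasoning and the named ANOVA concern spectral energy and not the CCMQ, and raw questionnaires are archived. That is fair, and it lowers the severity. It does not rescue row 2, the empty cell or the 39.29 gap, which remain under the per-subscale reading. Nor is this detail that an article leaves to a fuller document: the rule is stated, and stated wrongly.

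Four stronger readings are tempting, and the documents do not support them:

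- *Balanced becomes almost unattainable.* This needs the literal 0-800 sum. The section itself points away from it, and nothing shows the study scores that way.
- *The 30-point sentence flatly contradicts Table 4.* Thirty is also the table's lowest boundary, so the sentence can be read as the floor and the table as the detail. The fault is that the article does not say which.
- *Row 3 gives one person several constitutions, so chi-square counts are not independent.* The label is in the singular, and handling of multiple constitutions may be left to the analysis plan.
- *Participants are being misclassified.* The article does not show how scoring is run in practice.

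**Conclusion.** The concern holds as a defect in the printed rule. The row 2 contradiction, the undefined cell, the gap at 39.29 and the conflict between the header and the subscale criterion can all be seen within one section. The ambiguity over the 30-point criterion is real but weaker. The supported consequence is that participants can be misclassified or left unclassified if Table 4 is applied as printed. The number affected among the 250 planned is unknown, because the article gives no distribution of CCMQ scores. The carry-over to xiao-ke labels is also unknown, because no mapping from the CCMQ to those labels is given. The conclusion assumes 1-to-5 item scoring and, for reaching the empty cell, that shared items are not concentrated on one subscale. Severity is should-fix: the error is clear and the rule is used, but stored answers allow full correction.

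**What to change.** Before any constitution analysis:

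1. Define the second column as the highest adjusted score among the eight unbalanced constitutions.
2. Relabel row 2 so that it names the constitution scoring within that row's own band.
3. Write the bands as <30, 30 to <40 and ≥40, which places 39.29 in the middle band.
4. Add an explicit class, for example unclassified/indeterminate, for balanced <60 with all unbalanced scores <30, and report how many fall in it.
5. Check the 30-point sentence and Table 4 against the criteria they cite, and state whether 30 is the threshold for a tendency or for a classification.

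Then rescore the stored questionnaires under the corrected rule. The cost is a wording change and rescoring; no new data or visits are needed.

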#### Pulse Sphygmograph

The Asia Plus Pen Pulse Analysis System Model PPAS-93 (Asia Plus Biotech Co, Ltd) will be used to identify pulse profiles.

The PPAS-93 is a noninvasive device that comprises a high-precision pressure sensor pen and a pulse analyzer. The high-precision pressure sensor pen is a portable handheld pen that digitalizes the biological signal of the radial pressure pulse wave and provides graphical analysis using fast Fourier transformation. This electronic gadget incorporates a high-precision pressure sensor, a filter, an amplifier, and a signal recording card connected to signal analysis software. The sampling rate is 3000 Hz, and the frequency response is between 0.1 and 50 Hz.

With the participant sitting in a relaxed position, the *cun, guan,* and *chi* pulses of each hand will be assessed using the sensor pen with appropriate vertical pressure. The result will be recorded when the best spectrogram displays the highest amplitude. A summation of SE in the 0-10 Hz (SE_0-10Hz_), 10-50 Hz (SE_10-50Hz_), and 13-50 Hz (SE_13-50Hz_) frequency ranges will be obtained. Figure 1 depicts the pulse sphygmograph and its application output.

The time domain analysis examines the amplitude and shape of the arterial waveform such as surging, slippery, fine, and thready [30]. The pulse rate per minute can be determined by the number of waves in 6 seconds multiplied by 10. This will determine the rate such as a rapid or slow pulse. The frequency domain analyzes the variation of SE in the radial pulse waves [30]. The quantitative measures can assess the intensity and density of the SE, providing insight into the deficiency, repletion, coldness, heat, or dampness syndrome. An in-depth examination of both the time and frequency domains will be conducted to deduce the associated syndrome-etiology differentiation of *xiao-ke* (Table 2).

#### Tongue Diagnosis

The China Artificial Intelligence Health Status Identification System Model YZKJ-SMZY-1AI will be used to image and analyze the participant’s tongue. The noninvasive device captures the image of the tongue through an inbuilt camera supported by light-emitting diode lighting within the device within 15 seconds. A monitor connected to the imaging instrument would display real-time video feedback on the tongue’s position. Using an artificial intelligence system, the photographs of the face, tongue, and sublingual collaterals will be examined and compared with typical images of tongue analysis within 10 seconds. Figure 4 depicts the analytical details of the tongue, including the shape and color of the tongue, the texture and color of the tongue coating, the moisture level of the tongue, and the sublingual collaterals. The body constitution and syndrome differentiation will be analyzed and recorded. Figure 5 provides some examples of body constitutions and syndrome differentiation reported from the system. The results will be reconciled with the pulse diagnosis and CCMQ.

Before evaluation, the participants will be instructed to abstain from tongue scraping, smoking, and consuming caffeinated beverages such as coffee, tea, and cola, as well as dairy products such as milk, yogurt, and cheese, which may alter the tongue diagnosis.

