**Figure 1 figure1:**
[figure not shown]
(A) Location of cun, guan, and chi pulses on the radial artery. (B) Modern pulse sphygmograph and its application output in graphical and quantitative measures. (C) Application output indicating (a) palpating pressure; (b) pulse wave; (c) pulse rate per 6 seconds; (d) intensity and density of the wave spectral energy; and (e) quantitative measures of spectral energy, energy proportion, and spectral energy ratio.

Historical TCM references list 28 common pulse profiles seen in clinical practice [32]. Each radial pulse profile, with its distinct characteristics in the pulse depth, rate, waveform, density, and intensity, can reveal physiological or pathological changes in the human body [33]. For instance, Jeon et al [34] investigated pulse wave variation during the female menstrual cycle and reported that string-like or slippery and rapid pulses were seen. Subjective evaluations have been demonstrated to influence the diagnosis and treatments [31].

Aside from pulse diagnosis, tongue diagnosis is essential in distinguishing TCM syndromes. The practitioner examines the physiological and pathological changes in the tongue and associates them with specific viscera. Figure 2 provides the relationship between the tongue position and the viscera (*zang-fu*) systems. However, because observations are based on the physician’s judgment and can be easily influenced by environmental factors such as lighting and colored food, they can be highly subjective and inaccurate [35].

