#### Syndrome Differentiation

The syndrome differentiation of *xiao-ke* will be based on the objective assessment results analyzed from CCMQ, tongue, and pulse diagnosis regardless of the participants’ group status. Data collection under standardized conditions using contemporary diagnostic devices is expected to enhance stability and reliability in syndrome differentiation. This approach effectively minimizes bias and eliminates the necessity for blinding in our study design.

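### The protocol names coloured food as a cause of inaccurate tongue readings, but its list of things to avoid before tongue imaging leaves it out

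*Protocol article*

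**What the plan says.** In the Introduction, under Conventional TCM Diagnostic Techniques, the article explains why tongue observation by a physician is unreliable: observations "can be easily influenced by environmental factors such as lighting and colored food, they can be highly subjective and inaccurate".

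Under Methods, Tongue Diagnosis, the device "captures the image of the tongue through an inbuilt camera supported by light-emitting diode lighting within the device". Its analysis covers "the shape and color of the tongue, the texture and color of the tongue coating", as well as moisture and the sublingual collaterals. The preparation rule asks participants to "abstain from tongue scraping, smoking, and consuming caffeinated beverages such as coffee, tea, and cola, as well as dairy products", items "which may alter the tongue diagnosis".

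Under Syndrome Differentiation, the syndrome is based on the constitution questionnaire (CCMQ), the tongue and the pulse together. The article says of this standardised, device-based data collection: "This approach effectively minimizes bias and eliminates the necessity for blinding in our study design".

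**The concern.** The case for a device is that it removes the sources of inaccuracy that affect the physician's eye. The article names two such sources for the tongue and deals with only one. A stain changes the surface being photographed, so moving from eye to camera does not remove it, and the preparation rule itself accepts that intake can alter the device's reading.

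At stake are the group comparisons of tongue findings and, less directly, of syndromes. Standardised conditions are also the article's stated ground for doing without blinding. Blinding would not prevent staining, but an uncontrolled artefact that the article itself identifies weakens the claim that conditions are standardised.

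**Working it through.** No arithmetic gives the size of the effect, because the article states no staining rate and no error rate for the device. The check is a comparison of sections.

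1. **Sources of error named (Introduction).** Lighting and coloured food.

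2. **Control of lighting (Tongue Diagnosis).** Present: light-emitting diodes inside the device.

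3. **Control of coloured food (Tongue Diagnosis).** The list has four entries: tongue scraping, smoking, caffeinated beverages (coffee, tea, cola) and dairy products (milk, yogurt, cheese). The examples illustrate the beverage and dairy entries and do not open the list to other foods. Coffee, tea and cola are coloured, so part of the problem is covered. Coloured solid food, sweets and caffeine-free coloured drinks are not.

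4. **Other safeguards.** The article describes no mouth rinse, stain check or intake check at the visit. Glucose values come from the participant's own blood report (Health Evaluation), so the visit gives no reason to arrive fasted. The questionnaire on sugary food and drink records weekly intake, which does not show what was eaten just before imaging.

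5. **Does colour reach the syndrome?** Tongue colour signs in Table 2:

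| Syndrome | Tongue colour sign |
|---|---|
| Excess lung heat and fluid deficiency | Red tip, thin yellow coating |
| Excess stomach heat | Yellow coating |
| Qi and yin deficiency | None listed |
| Kidney yin deficiency | Red tongue |
| Yin and yang deficiency | Pale, white tongue |

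Yellow coating appears in 2 of 5 syndromes, and some tongue colour in 4 of 5. All of these stand in the column of other symptoms, not among the main clinical manifestations.

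6. **What is not reached.** The SE_13-50Hz comparison uses the pulse device alone.

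7. **Room for change.** The Abstract reports 140 enrolled by July 15, 2024, out of 250. At that date at most 250 − 140 = 110 participants remained to be imaged under a corrected instruction.

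**The case against.** The strongest reply is that the Introduction sentence concerns the physician's judgment. It motivates using a device and commits the Methods to nothing, and a journal article need not print every participant instruction. This stands in part: the two sections do not contradict each other in the strict sense. But the article does print the preparation rule, and that rule omits the one food-related cause the article names. This is a stated rule with a gap in it, which is different from a detail left to the full protocol.

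The reply is right on several stronger readings that a reader might infer:

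- **The missing time interval is an error.** The article says only that the instruction is given before evaluation. The interval may well stand in the full protocol (version 1.8), which is not shown, so its absence is no finding.
- **Yellow coating defines the heat syndromes.** Table 2 makes it an accompanying sign. The main manifestations there are polydipsia, and polyphagia with weight loss.
- **A stain produces a wrong syndrome.** The tongue result is reconciled with the pulse and the CCMQ, and colour is only one of several tongue features. For the heat syndromes a stain matters only if it reads as yellow coating or, for lung heat, as a red tip.
- **The error differs between groups.** People with diabetes might eat fewer sweets than controls, but the article gives no data on this, nor any staining rate.

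**Conclusion.** The point holds in a limited form. The printed list allows a fully compliant participant to be imaged after coloured food or a caffeine-free coloured drink, although the article itself says coloured food makes tongue readings inaccurate. Because the device analyses tongue and coating colour, this can add error to the tongue comparisons and, diluted by the CCMQ and pulse, to the syndrome comparisons.

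The size and direction of that error cannot be derived from the article. Any percentage of stained participants would be a guess, and a bias between groups is possible but not shown. The conclusion assumes that the full protocol does not already extend the list and that the device does not detect staining; the article indicates neither. The SE_13-50Hz comparison is not affected. This is a modest weakness of measurement that is cheap to correct.

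**What to change.** In Methods, Tongue Diagnosis, add coloured foods, sweets and coloured drinks to the list. Have the operator record at the visit whether any listed item was recently consumed, using whatever time window the full protocol sets, or one stated window if it sets none.

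Keep every participant in the main analysis, and repeat the tongue and syndrome comparisons without flagged participants as a sensitivity analysis, reporting the number flagged in each group. Setting coating colour to missing would be a poorer remedy. The device's own algorithm derives constitution and syndrome from the features it identifies, so the stained colour would already be in that output. It would also conflict with the statement under Data Management and Monitoring that no data will be left out.

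The cost is one sentence in the instructions, one tick-box and one repeated analysis. The downside is that participants already imaged followed the present list and have no flag. Because each group closes separately once it reaches 50, enrolment period may be confounded with group, so a simple before-and-after comparison could mislead. Report the date of the change and the number in each group imaged before and after it. If imaging is already complete, report the gap as a limitation.
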